### Register data

All data will be drawn from Danish national registers. The study will include information on health care services (somatic and psychiatric inpatient and outpatient care, including emergency services and diagnosis related groups (DRG), general practitioners, dentists and other medical specialists, medical prescriptions) and social services. Differences in utilisation of health care will be reported in natural units and costs, while differences in utilisation of social services will be reported in natural units. All elements included in the analyses are described in more detail in Table 2.

**Table 2 tab2:** Components included in the economic evaluation.

Costs	Definition	Source
Hospital costs	Inpatient, outpatient, and emergency room contacts in somatic and psychiatric hospitals, valued with Danish national diagnosis-related groups (DRG)-tariffs.	The National Patient Register with DRG and outpatient tariffs (37, 38).
Primary healthcare costs	Contacts to general practitioners, practising specialists and other health care professionals reimbursed (or partly reimbursed) by the Danish National Health Service, e.g., dental care or psychological treatment. Costs are valued with national service tariffs.	The National Health Service Register (39).
Prescription pharmaceuticals	The full price (regardless of subsidies etc) of prescription drugs purchased in Danish pharmacies.	The Pharmaceutical Database (40).
Transfer payments	Cash benefits, early retirement pension, education benefits, other transfers	DREAM database
Costs of labour market interventions	All interventions initiated by the municipal job centres: counselling, mentor support or vocational rehabilitation interventions.	Data will be obtained from the Danish Agency for Labour Market and Recruitment.
Social service costs	Alcohol abuse treatment; drug abuse treatment, day-care; drug abuse treatment; temporary housing; long-term housing; soc. support in housing; public housing; soc.pæd. Support in one’s own home; subsidies for personal and practical help; disability assistance scheme; companion scheme; sheltered employment or activity; and social services	Data will be obtained from Statistics Denmark
Intervention costs	Costs of a counselling session at headspace will be calculated	Data will be obtained from headspace Denmark.
Police, judiciary, and penitentiary	Imprisonment; conviction for violent and moral crimes; conviction for burglary, theft, and vandalism; conviction for traffic law and other special laws	Data will be obtained from the Danish system of criminal statistics
Tax on income	Tax on transfer income, employment	e-income register
Education	Youth education and higher education	Danish Education Registry

### Cost-effectiveness analyses

The time horizon of the evaluation will be 3 years from the first contact to *headspace*. To evaluate cost-effectiveness, the incremental cost-effect ratio (ICER) will be estimated (27). The ICER represents the cost differences between the *headspace* group and the control group divided with differences in outcome measured by labour market contact/educational attainment. Nonparametric bootstrapping will be used to estimate confidence intervals of the mean differences of the groups. Predicted ICERs will be depicted on cost-effectiveness planes to show uncertainty therein. A cost-effectiveness acceptability curve will be generated to assess the probability of *headspace* being cost-effective when the decision-maker is willing to incur additional costs for an extra point increase in outcome up to a given threshold.

## Study 3: process evaluation

The aim of the process evaluation is to investigate the implementation, context, and mechanisms of impact of the key activities in the *headspace* intervention. The focus of the study is the four key activities of *headspace:* (1) individual counselling with *headspace* volunteers, (2) bridging to established social and health services, (3) chat services (counselling and referral to individual counselling) and (4) community engagement where counsellors engage in community activities to obtain visibility regarding *headspace* and possibly also reduce stigma towards mental vulnerability. In line with the MRC guidelines (28), and as recommended by Moore et al. (29), the study will address the three aspects of the *headspace* intervention, implementation, mechanisms of change and context, through a multi-stakeholder perspective (Table 3).

**Table 3 tab3:** Overview of research questions and data collection methods in the process evaluation of the headspace intervention.

Aspect of process evaluation	Research question	Data collection methods (what)	Data source (who)	Data collection (how)	Data collection period
Implementation	What is implemented in terms of the key activities counselling, chat counselling, bridging to other services and community engagement?	Forms registering headspace key activities	The forms are filled out by the headspace counsellors after conducting key activities and send to the headspace organisation administration unit	Data on key activities for all headspace centres and displayed for each of the four headspace centres and the chat centre participating in the process evaluation will be sent from the administration unit to the researcher on request.	Data is collected continually in the study period (2023)
	Who are reached?	Forms registration service users	The forms are filled out by the headspace counsellors after counselling and send to the headspace organisation administration unit	Same as above	Data is collected continually in the study period (2023)
	How is delivery achieved?	Participant observation and interviews	Four headspace centres and one national chat centres Managers, counsellors (paid and volunteer), assertive professionals and service users.	Trained research centre attends key activities and other activities in headspace centres (3 days pr. centre) Key informant interviews with managers and assertive professionals Focus group interviews with counsellors at the headspace centres. Service users are recruited for interviews	Data is collected from June 2023 until January 2024
Mechanisms of impact	How do the service users respond to and interact with the intervention?	Participant observation of key activities and interviews	Service users, counsellors	Trained researchers participate in counselling sessions in the 4 headspace centres and in the chat centre when the service user provide consent. Service users are invited to interviews with researchers about their experiences with the headspace intervention	In the study period (June 2023–January 2024)
	How do the key activities create the intended effects on services users’ mental health, loneliness, and self-efficacy?	Interviews	Service users		
	Which unexpected effects/consequences might there be?	Interviews	Service users		
Context	How do contextual factors (legal, organisational, cultural, geographical, and political) affect the implementation and the outcomes of the intervention?	Participant observation, interviews	National manager, cross centre managers, assertive professionals, counsellors	Interviews are conducted in conjunction with participant observations at the headspace centres. If needed key informant interviews will be conducted with additional cross centre managers and service users (until saturation is achieved)	During the study period
	How do services user’s contextual factors affect the implementation and the outcomes of the intervention?	Participant observation, interviews	Counsellors, service users		

### Study participants and data collection methods

The process evaluation will predominantly deploy a qualitative research methodology, as it is suitable for investigating how the headspace intervention is implemented to produce its intended outcomes and how interactions, dynamics, and contextual factors influence implantation (29). This will be done by investigating the stakeholders’ interactions, experiences, and perspectives on the process. The stakeholders in this study are identified as the service users, the implementers, and the management of headspace Denmark. Thus, study participants are young people using headspace counselling, the counsellors (paid counsellors and volunteers) the assertive professionals, and the cross-centre management.

To explore and capture the complexity and nuances of how the intervention is delivered, the data collection will take place in four headspace centres in Denmark, and in the national chat enter and utilise a combination of data collection methods: semi-structured interviews (individual and focus group) and participant observations.

### Implementation

Implementation can be defined as “the process through which interventions are delivered” (29). The delivery of the four key activities (counselling, chat counselling, bridging to other services, community engagement) in *headspace* is described through semi-structured interviews (individual and focus group) and observations of the stakeholders in the intervention: volunteer counsellors, paid counsellors, chat counsellors, assertive professionals, and managers (both cross-centre management and the national *headspace* CEO). Factors that support or impede the implementation of these four activities (e.g., training, knowledge sharing) are investigated. Participant observations will be used to gain a more in-depth understanding of how the activities are practised and how that adds nuances to the described experiences from the interviews (30). The implementation of key activities will also be described through interviews with service users and descriptions of their experiences in the *headspace* intervention. In addition to investigating the intervention delivery processes, the *headspace* intervention’s reach and dose will be described quantitatively with register data from the *headspace* centres.

### Mechanisms of impact

Mechanisms of impact are defined as “the intermediate mechanisms through which intervention activities produce intended (or unintended) effects” for the individual service user (29). This study will describe possible mechanisms by which the key activities might create effects on service users’ loneliness, wellbeing, self-efficacy, and mental health (see Figure 1). The study will emphasise the perspectives of the service users and investigate their (possible) progression after engaging with *headspace.* If feasible, service users will be interviewed twice. The first interview is expected to take place right after the first counselling session. Previous evaluations have shown that service users engage in 2.7 counselling sessions on average (15). Follow-up interviews are expected to be conducted after the last counselling session and on average 4 months after the first session. This relatively short follow-up time (compared to study 1) will ensure that experiences regarding *headspace* are not too far away in memory and thus provide longitudinal information about the life course of each service user and their experienced benefits (or negative experiences from interacting with *headspace* personnel).

### Context

Context is broadly understood as “factors external to the intervention which may influence its implementation, or whether its mechanisms of impact act as intended” (29). Contextual factors that might be relevant for the delivery and function of the *headspace* intervention can both be related to the context of the service user, the political and geographical context, the organisational context, the socio-economic context, legal and cultural context (31). Some variation in the way the *headspace* intervention works in different municipalities with different demographical and organisational settings is expected. To be able to address how these contextual factors might influence the implementation and functioning of the intervention, we will apply a sampling strategy with a high variation (for instance centres located in urban vs. rural areas) between cases (32). By understanding how the intervention possibly works differently or is implemented differently in different municipal contexts can give clues for how context affects implementation and mechanisms of impact (31).

### Data analysis and integration

The quantitative data will be analysed, using descriptive statistics to provide information on the reach and dose of delivery of the *headspace* intervention. The data will be presented for all *headspace* centres in Denmark and the four *headspace* centres and the national chat centre participating in the process evaluation. The qualitative data is recorded digitally and transcribed ad verbatim, using NVivo software. The transcripts will be analysed thematically, using both a deductive approach with the preliminary programme theory as a point of the departure and an inductive approach for allowing unforeseen information and emerging themes to come forward. The findings of the process evaluation will not be reported to the centres continuously or used for quality improvement purposes, as the effectiveness evaluation attempts to evaluate the *headspace* intervention under “natural” circumstances. Thus, this process evaluation can be characterised as summative.

### Ethics statement

The evaluation will be conducted in accordance with the present protocol, the Helsinki Declaration in its latest form, good clinical practise guidelines, and national and EU legislation on data management. The effectiveness evaluation, the cost-effectiveness evaluation and the process evaluation are not expected to pose any known adverse effects. For all studies, informed consent will be utilised in accordance with Danish and European legislation, and all service users who participate in the survey of questionnaires, observations and/or interviews will be secured anonymity (Privacy no. P-2022-602). Since the evaluation is not a biomedical study and because the intervention is conducted at the *headspace* centres, the protocol does not require acceptance from the Ethics Committee in the Capital Region of Denmark (Case number of correspondence with the Ethics Committee: 21061429).

## Discussion

This paper presents the study protocol for three studies: an effectiveness, cost-effectiveness, and process evaluation of the *headspace* intervention in Denmark. Because the *headspace* model has achieved national endorsement and is fully implemented in 30 municipalities throughout Denmark there is an urgent need for scientific knowledge about the effectiveness of the intervention. The evaluation will contribute with new, important knowledge that not only will benefit *headspace* Denmark, but also contributes with new knowledge and documentation targeted to international mental health promotion initiatives, primary and lower secondary schools, educational institutions, and municipal social initiatives.

Overall, the three studies presented in this paper will bring new knowledge about the potential contribution and impact of *headspace Denmark* as a preventive intervention and contribute with new and useful knowledge about the possibly derived effects of counselling sessions in *headspace*. The large number of participants, as well as the establishment of a matched control group and long-term follow-up, makes it possible to provide more reliable and accurate estimates compared with previous studies.

The economic evaluation will contribute new knowledge about the cost-effectiveness of *headspace* Denmark, which can be used for a more nuanced societal prioritisation of resources allocated to vulnerable young people. Finally, the process evaluation will thoroughly describe the key activities of the Danish *headspace* intervention and document how these can be implemented in a local context and how they might create the expected effects on youth mental health and wellbeing. This valuable information can in a future perspective be used to further qualify the *Danish headspace* model.

### Methodological challenges

Despite a comprehensive study design, some methodological challenges exist. The main limitation of this study is the design—that the effectiveness evaluation of the Danish *headspac*e model is not performed as a randomised controlled trial, as it was not practically possible. The second most important limitation is difficulties in identifying a control group. We have tried to solve that by matching on failure to thrive, but we cannot identify the most important variable: help-seeking behaviour. Therefore, there is a risk that participants in the control group might have a better prognosis because they do not feel quite as bad (even though they have the same wellbeing and other match factors). There may also be a risk that participants in the *headspace* group have a better prognosis because they were able to seek and find help. There is also a risk that young people in the control group seek help from *headspace* centres after taking part in the study. Although the members of the control group live outside the catchment areas of the headspace centres, there might be a chance that some individuals contact the centres or the national chat centre during the study period. This introduces a risk of contamination, as both groups will be exposed to the intervention investigated. Young people in the control group who need help can use available social and health services, and mental health support offered in their community, but no signposting to specific organisations/services is provided in the material sent to the participants.

A potential pitfall in the effectiveness evaluation pertains to selection bias and the dynamics of outcomes before participation in the study (33). Young people’s mental health and wellbeing may be volatile with emotional ups and downs rather than persistent with the same levels of wellbeing over time, for instance shown in a study by Tegner Anker et al. (34). Youth would primarily seek help at “mental downturns,” that is at times with high level of emotional distress, there will be a regression to the mean, that might be difficult to identify in the control, thus posing a risk that natural improvements will be interpreted as effectiveness of the *headspace* intervention. While analysing the data, differences between the groups on all baseline outcomes will be tested for statistical significance. The analyses for differences between groups will be adjusted for any baseline differences with a *p*-value below 0.05.

Participants in the *headspace* group and the control group are matched on individual-level characteristics only. At the beginning of the data collection period, there were headspace centres in 22 out of the 100 municipalities of Denmark, meaning that it was not hard to identify controls. There were headspace centres is the four largest cities of Denmark (Copenhagen, Aarhus, Odense, and Aalborg) but not in some of the other larger cities such as Silkeborg or Kolding. There could be unobserved municipality-level factors potentially affecting the treatment effect estimates, e.g., related to urban density or distance to urban centres. We have, however, seen no substantial problems for the matching algorithm to identify comparable controls on the observed factors. We would also, from a pragmatic point of view, expect important municipality-level differences to be captured by the range of individual-level matching factors used (e.g., social status).

A limitation in the effectiveness evaluation may be that not all the register-based data will be completely updated at the time of matching. However, historical data such as national school tests, and wellbeing at primary school is expected to be prognostic and relevant to use in the matching. Moreover, many but not all the registers are updated in real-time such as the National Patient Register, which is available from The Danish Health Data Authority after a few days. Moreover, the matching procedure will be repeated before conducting the 3 years effect analyses, where all data will be updated at the time of matching. A limitation in using surveys as data collection methods is that respondents constitute a sample of the population rather than the whole population of *headspace* service users. As *headspace* collects basic information on service users, a supplementary analysis will be performed, comparing *headspace* users accepting registration on unique personal ID with *headspace* users not accepting to give their personal ID and participate in this evaluation. The comparison includes age, gender and additional information on social and health-related problems faced by participants. The process evaluation must consider, the flexibility of the *headspace* intervention. Key principles in the *headspace* model necessitate a person-centred approach where the consultation is guided by what is on the mind of the young person seeking support. Also, the counsellors are encouraged to take ownership in the local *headspace* centres and initiatives to develop local services. Although the sampling strategy is based on maximal variations with respect to factors such as urban/rural locations, new/old centres and high/low community engagement, there might be other important factors not considered in the selection of centres that affect how the *headspace* intervention is implemented and works, thus comprising the external validity of the findings.

Also, the evaluation’s limitation pertains to potential bias in the volunteer-based counselling model offered in the *headspace* centres, which may affect issues related to the outcomes and implementation. The young people seeking counselling in *headspace* may be characterised by distinct features (e.g., related to motivations, and skills) compared to the whole population of youth with mental health problems. Moreover, the young people who participate in the studies might be different from the group of service users in *headspace.* They may already have positive attitudes and expectations towards counselling. This potential selection bias might lead to an overestimation of the effectiveness of the counselling offered in *headspace* (35). Another limitation of the volunteer-based counselling model is that the counsellors posit varying levels of skills and competencies, which may lead to inconsistent quality of counselling. Although training is provided to the counsellors before and during their involvement in *headspace,* there is a risk that the effectiveness of the counselling model depends on the counsellors` experiences rather than the model itself. To ensure that the headspace intervention is implemented as intended and strengthen the quality of the counselling services provided in headspace centres, a fidelity scale will be developed based on the findings from the process evaluation (36).

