### Data analysis

#### Sample size

A very conservative estimate of 1,900 participants with complete data at both baseline and follow-up (400 in *headspace* and 1,500 among controls), will provide 90% power to detect standardised mean differences of 0.18 in a two-sided *t*-test. This corresponds to 0.22 points on the WHO-5 Wellbeing Index, 1.16 points on the General Self-Efficacy scale and 0.36 points on Cantril’s Ladder. However, the statistical power might be degraded for analyses relying on multiple imputation because of the expected substantial proportion of missing data. The registry-based outcomes measured at 3 years of follow-up are unaffected by missingness and will have an expected 10,000 controls and 1,500 cases. This will provide statistical power sufficient for detecting small effect sizes, e.g., 83% power for detecting a 12.5 vs. 10% difference on a binary outcome.

Baseline characteristics for the two groups will be reported using means and standard deviations for numeric variables and count (n) with percentages for categorical variables. Mean difference from baseline to follow-up will be presented for both the *headspace* and the control group for all the included outcome measures. For normally distributed continuous outcomes a linear regression will be conducted to test the differences between the two groups. For non-normally distributed outcomes a proportional odds model will be used. The analyses for differences between groups will be adjusted for any baseline differences exceeding a predefined threshold. Moreover, subgroup analyses will be conducted where all analyses will be stratified for age (≥18 years). Missingness will affect the survey measures recorded at baseline and follow-up. Missing data will be handled using multiple imputations, possibly in combination with inverse probability weighting of observations (26). Imputation variables will be included from the complete (or near-complete) and co-occurring registry-based data observations as well as from all survey data collected up to the timepoint of the measure being imputed. A detailed statistical analysis plan (SAP) is also published and available at: https://archive.org/details/osf-registrations-9kzfd-v1.

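### Adjustment for baseline outcomes depends on a p<0.05 test; the baseline score should always be in the model, mainly for precision

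*Protocol article*

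**What the plan says.** The rule appears twice in the protocol article.

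- **Methodological challenges (Discussion).** After describing selection bias and regression to the mean, the text says that "differences between the groups on all baseline outcomes will be tested for statistical significance". The next sentence says that the analyses of group differences "will be adjusted for any baseline differences with a *p*-value below 0.05".
- **Data analysis, Sample size.** "The analyses for differences between groups will be adjusted for any baseline differences exceeding a predefined threshold". The threshold is not given there.

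The models are in the same Sample size text. "For normally distributed continuous outcomes a linear regression will be conducted to test the differences between the two groups", and "For non-normally distributed outcomes a proportional odds model will be used". Neither sentence names a covariate that is always included. The text also says that "Mean difference from baseline to follow-up will be presented for both the" groups, so the outcome analysed could be the 6-month score or the change from baseline; the article does not say which.

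The section on matching the control group adds a safeguard. Once all baseline data are in, matching is repeated on the whole pool with the self-reported outcomes among the matching parameters, accepting fewer controls.

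**The concern.** A test of baseline difference answers the wrong question here. Nobody was randomised, so an imbalance does not stop confounding the comparison because it misses p<0.05, and one does not become important because a large sample makes it significant. The rule also lets the observed data choose the estimator, and the final test takes no account of that choice.

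Two things are at stake at 6 months. First, a real but non-significant gap stays in the estimate. Second, good matching makes significant baseline tests rare, so the rule will usually select the unadjusted model, although every baseline score is collected and would reduce the residual variance.

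**Working it through.** **Inputs.** From Data analysis, Sample size: "A very conservative estimate of 1,900 participants with complete data at both baseline and follow-up", split as "400 in *headspace* and 1,500 among controls"; 90% power for a standardised difference of 0.18, two-sided t-test. From the matching section: a possible 2:1 ratio of controls. Assumed because the article does not give them: alpha 0.05; baseline to follow-up correlation r from 0.3 to 0.7; a true baseline gap of 0.10 SD for the adverse case.

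**1. The plan's own figure.** SE = √(1/400 + 1/1,500) = 0.0563 SD. Power = Φ(0.18/0.0563 − 1.96) = 89.2%. The stated 90% reproduces.

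**2. What the screen lets through.** The largest non-significant gap is 1.96 × 0.0563 = 0.110 SD, and 0.110/0.18 = 61% of the target. At 1,500 versus 3,000 it is 1.96 × √(1/1,500 + 1/3,000) = 0.062 SD. The same imbalance is therefore ignored or adjusted for according to sample size. At 400 versus 1,500 a true gap of 0.05, 0.10 or 0.15 SD goes unflagged with probability 86%, 57% or 24%.

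**3. What an unadjusted gap g does.** If headspace users start worse by g, the bias is r × g against headspace on follow-up scores, and (1 − r) × g in its favour on change scores.

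**4. The rule against always adjusting.** Always adjusting multiplies the SE by √(1 − r²), so power = Φ(0.18/(0.0563 × √(1 − r²)) − 1.96). The test-then-adjust rule was simulated at 400 versus 1,500 (normal approximation, 2,000,000 replicates per setting).

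Power at 0.18 SD with no true baseline gap:

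| r | Rule, follow-up score | Rule, change score | Always adjusted |
|---|---|---|---|
| 0.3 | 89.6% | 78.7% | 91.8% |
| 0.5 | 90.2% | 90.2% | 95.8% |
| 0.6 | 90.6% | 95.3% | 97.9% |
| 0.7 | 90.9% | 98.7% | 99.4% |

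Mean bias and type I error with headspace users 0.10 SD worse at baseline (positive bias favours headspace):

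| r | Rule, follow-up score | Rule, change score | Always adjusted |
|---|---|---|---|
| 0.3 | −0.011 SD, 5.4% | +0.025 SD, 6.1% | 0, 5.0% |
| 0.5 | −0.018 SD, 5.9% | +0.018 SD, 5.9% | 0, 5.0% |
| 0.6 | −0.021 SD, 6.2% | +0.014 SD, 5.7% | 0, 5.0% |
| 0.7 | −0.025 SD, 6.4% | +0.010 SD, 5.5% | 0, 5.0% |

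With rounding and simulation error, type I error is about 5.3% to 6.5%. With no gap the rule is slightly conservative (3.6% to 4.8%). With the gap, r = 0.6 and follow-up scores, power under the rule is 84% against 98% if always adjusted. On change scores both are 98%, though the bias towards headspace helps the rule there.

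**5. Regression to the mean.** Suppose headspace users enrol in a transient dip d that controls do not share, and the true effect is zero. The change score is then biased by +d and the baseline-adjusted estimate by +r × d. With d = 0.10 and r = 0.6 these are +0.10 and +0.06 SD, and the always-adjusted test rejects 27% of the time. The unadjusted follow-up comparison is unbiased in this case.

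**The case against.** The other side has a good case on size.

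- **Re-matching is the main safeguard.** Matching again on the self-reported outcomes should leave little imbalance, and nothing in the article shows that a 0.10 SD gap would survive it. This stands, so the bias is probably modest. It does not remove the point. The match is on a summary score within a caliper, dropout can reopen gaps, and the precision loss occurs under perfect balance.
- **The numbers depend on unstated choices.** The article gives neither r nor the outcome coding. On change scores with r = 0.6 the no-gap loss is only 95% against 98%; on follow-up scores with r = 0.3 it is 90% against 92%. This stands, hence the ranges.
- **400 versus 1,500 is the plan's conservative case.** With more responders the unflagged gap shrinks. This also stands.
- **The rule roughly meets the planned 90% power on follow-up scores.** True when there is no gap; the extra power is then an improvement and not a rescue.

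A reader might infer that the two sections contradict each other. They need not: the predefined threshold under Data analysis can simply be the p<0.05 stated in the Discussion. The two statements are unaligned, not shown to conflict.

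A reader might also infer that always adjusting settles the regression-to-the-mean problem, or that adjusted and change-score estimates bracket it. Step 5 shows otherwise: under a transient dip both err in favour of headspace, so the truth lies outside the pair. The p<0.05 rule gives no reliable protection either, since it adjusts exactly when the dip is large enough to be significant.

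The separate SAP, which the article says is published, was not available and may specify a different rule. The article's wording would then still need to be aligned with it.

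**Conclusion.** The point holds as a badly chosen stated rule, not as an omission. The firmer loss is precision in the 6-month survey analysis: with no gap, 90-91% power on follow-up scores or 79-99% on change scores, against 92-99% with the baseline score always included. The bias is smaller and less certain: about 0.01 to 0.025 SD on average if a true 0.10 SD gap survives re-matching, against headspace on follow-up scores and in its favour on change scores when its users start worse.

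All of this assumes r between 0.3 and 0.7, alpha 0.05 and 400 versus 1,500. It applies to the linear model only; in the proportional odds model, adjustment also changes the conditional effect being estimated. The documents do not support a claim that the rule invalidates the comparison. Confounding by help-seeking and regression to the mean remain the larger threats under either rule. Severity: should fix.

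**What to change.** Delete the p<0.05 trigger under Methodological challenges and the threshold wording under Data analysis. State the same rule in both places: each survey outcome is analysed with its own baseline value always in the model, whatever imbalance is observed. Describe balance by standardised mean differences, without significance tests.

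The unadjusted difference may be reported as a sensitivity analysis, without claiming that the two estimates bracket regression to the mean. Say plainly that baseline adjustment removes neither that threat nor confounding by help-seeking.

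The cost is a wording change in the protocol, and in the SAP if it carries the same rule. No new data are needed, because the baseline scores are already being collected.
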